### 2.6. Informed Consent

Members of the research team will give participants detailed and comprehensive information about the study and help participants to make an independent decision with regard to their participation in the study. Any potential participant will undergo a process of informed consent. If a participant agrees, he/she will sign a consent form approved by the Internal Review Board at the University of Kansas Medical Center. Throughout the process, members of the research team will avoid any coercion and ensure the participant’s confidentiality.

### 2.7. Randomization and Double-Blinding

All participants will be assigned a randomly generated 6-digit alphanumeric code after consenting to the study. Assignment to either experimental or control group will be determined by a computer-generated random code (e.g., 0 or 1) in a 1:1 ratio. All participants and outcome assessors will be blinded to the group assignment and intervention. Collected data will be stored on the secured server provided by the University of Kansas Medical Center. All individual information will be stored in the de-identifiable form.

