Although it may be impossible to stop neurodegeneration in PD, many therapeutic approaches have been developed to alleviate symptoms in PD. Qigong is a mind-body exercise that has shown benefits on symptoms in PD. A study involving individuals with mild to moderate PD demonstrated a significant improvement in sleep quality [16]. In our feasibility study in a single-arm design (n = 7), a 6-week Qigong exercise program demonstrated an improvement in sleep quality measured by Parkinson’s Disease Sleep Scale-2 (PDSS-2), in which the results showed sub-scores of PDSS-2 were significantly improved or showed a trend of improvement including motor symptoms at night (*p* < 0.05) and disturbed sleep (*p* = 0.06) in individuals with PD [17]. Our recent pilot study, a randomized controlled trial (RCT), in individuals with PD showed a significant improvement in sleep quality, including PD symptoms at night (*p* < 0.05) and total PDSS-2 score (*p* < 0.001), after practicing the Qigong exercise for eight weeks (2-week training + 6-week Qigong exercise) [18].

The exact mechanism of Qigong exercise behind clinical improvements observed in patients with PD has not yet been completely understood. A possible mechanism of Qigong exercise may involve biological pathways related to neuroinflammation. The deep abdominal breathing may stimulate serotonin pathways by stimulating enterochromaffin cells that release serotonin [19] and interact with pro-inflammatory cytokines that contribute to neuroinflammation in the brain [20]. Our recent pilot study suggested potential benefits of Qigong exercise through changes in inflammation status, in which the results showed a significant decrease in serum level of TNF-α from 13.8 ± 0.6 to 12.3 ± 1.6 (*p* < 0.05) that was significantly correlated with changes in sleep quality and serum TNF-α level (R^2^ = 0.62) [18]. In various medical conditions, mind-body exercises such as Yoga, Tai Chi, and Qigong improved the immune system [21]. Particularly, past studies reported the benefits of Qigong exercise on immunological functions in healthy people [22] and individuals with cancers [23,24,25]. 

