## 2. Study Design and Aims

### 2.1. Study Design

We designed a double-blind RCT involving 60 individuals with PD (Figure 1). The participants will be randomly assigned to either an experimental (n = 30) or control (n = 30) group. Each group will have group exercise meetings (nine times in total; weekly meeting for first six weeks and then biweekly meetings for next six weeks) throughout the 12 weeks of the intervention period. Participants will be blinded to their group assignments until the end of the study. At baseline, all outcome measures and demographic variables including age, sex, ethnicity, years of education, disease duration, and medications will be collected. After the baseline assessments, participants in both groups will have a 12-week intervention period, including three weeks of training and nine weeks of exercise. The duration of the intervention will be longer than our two previous studies to provide more structured training sessions and longer intervention time [17,18]. During the training period, participants in the experimental group will learn the Qigong exercise, whereas those in the control group will learn the sham Qigong exercise. During the exercise period, participants will continue to practice what they will have learned during the training period. Throughout the 12-week intervention period, all participants will be asked to perform their assigned exercise (Qigong or sham Qigong exercise) twice a day at home, in the morning and evening, attend group meetings (weekly meeting for first six weeks and then biweekly meetings for next six weeks) and keep an exercise diary. The exercise diary includes daily checklists (morning exercise (yes/no), evening exercise (yes/no), and other exercise more than 0.5 h (yes/no)), subjective scales (sleep quality (1–5), fatigue level (0–10), and pain level (0–10)), and participant’s note for any unusual events. Within two weeks after the completion of the 12-week intervention, post-intervention assessments will be conducted, which are the same as the baseline assessments. The assessments will be completed again six months after the end of the intervention period.

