#### 2.4.2. Exclusion Criteria

The study exclusion criteria include (Table 1): (1) Mini Mental State Examination score <24 [31], (2) neurological diseases other than idiopathic PD including other forms of parkinsonism, uncontrolled or significant cardiovascular diseases, orthopedic, balance, or medical problems, (3) prior major head trauma with loss of consciousness, (4) deep brain stimulation, and (5) expected change in PD medications or non-motor symptom medications (e.g., sleep, anxiety, and depression medications) that may affect the results of the proposed outcome measures over the course of the study.

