### 2.5. Recruitment and Screening

Participants will be recruited primarily from the Parkinson’s Disease and Movement Disorder Center at the University of Kansas Medical Center, in which approximately 200 new and 1400 returning individuals with PD are seen annually. Among individuals with PD being seen, we expect about two thirds will meet our recruitment criteria. Individuals who indicate an interest to participate in research will be contacted by a member of our team. Physician’s permission will be obtained prior to an individual’s participation in the study.

An initial screening will be conducted via phone by members of the research team using a screening script (Table A1).

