### 3.2. Control Group

To match with the experimental group in terms of the intensity of activities and duration of the study, a sham Qigong exercise will be utilized. The sham Qigong instructor will be blinded to the study hypothesis to avoid a potential bias and minimize any influence on study outcomes. The sham Qigong exercise consists of the same mild body movements as the Qigong exercise. However, participants in the control group will not be taught abdominal breathing techniques with six healing sounds and meditation during the exercise. The format of Sham Qigong exercise program will be the same over the 12-week intervention. The control group will have group meetings separately from the experimental group, once per week in the first six weeks, and every other week the last six weeks. During group meetings, the sham Qigong instructor will assess the performance of each participant and discuss relevant issues that are the same topics for the experimental group meeting for about an hour. The same baseline, post-intervention, and 6-month follow-up assessments will be conducted. This group will be asked to practice the sham Qigong exercise twice a day at home and keep an exercise diary.

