## Appendix A

**Table A1 medicines-06-00013-t0A1:** Phone screening script.

Date:	
Subject Name:	
1. Assuming patient is available for answering questions, ask the following questions:	
2. Are you able to participate in a study which requires the practice of mild daily exercise and **about 11** visits to KU Medical Center over the course of 14 weeks? Specifically there will be 2 visits for assessment prior to and immediately following the study, 9 visits of group exercise sessions during the study. Will this work for you? **YES**—move onto question #3 **NO**—thank them for their time and let them know they are not eligible for this study at this time	
3. Have you been diagnosed with primary (or idiopathic) Parkinson’s disease? **YES**—move onto next question **NO**—thank them for their time and let them know they are not eligible for this study at this time	
4. Are you between the ages of 40 and 75? **YES**—move onto next question **NO**—thank them for their time and let them know they are not eligible for this study at this time	
5. Treatments a) Are you aware of any intentions of changing your medication or dosages over the next three months? **YES** **NO** b) Does your treatment include Deep Brain Stimulation (DBS)? **YES** **NO** **Part a) or Part b): YES**—thank them for their time and let them know they are not eligible for this study at this time **NO**—move onto next question	
6. Have you been diagnosed with any other medical problems (neurological, orthopedic, etc.) that interfere with your ability to do mild body movements and/or follow instructions? **YES**—thank them for their time and let them know they are not eligible for this study at this time **NO**—move onto next question	
7. Are you able to give a simple blood test which includes 30ml (about 1 oz.) of venous blood collection at pre- and post-testing? **YES**—move onto next question **NO**—thank them for their time and let them know they are not eligible for this study at this time	
8. Can you be contacted for participation in the study within two weeks? **YES**—move onto next question **NO**—When will you be available for the study ___________________	
9. What is the phone # and email address to contact you in the next three months? Cell phone # (if available): Email address:

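### The eligibility rules admit people who already know Qigong, which puts participant blinding and the sham contrast at risk for those participants on the self-reported primary outcome

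*Protocol article*

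**What the plan says.** The protocol article makes the blinding claim twice. Section 2.1 says "Participants will be blinded to their group assignments until the end of the study", and section 2.7 says "All participants and outcome assessors will be blinded to the group assignment and intervention".

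Section 3.1 describes the active exercise as gentle movements combined with meditation, abdominal breathing and six uttered sounds. Under section 3.2 the sham uses the same movements, but "participants in the control group will not be taught abdominal breathing techniques with six healing sounds and meditation during the exercise".

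Section 2.4.2 lists five exclusions and ends with "3) prior major head trauma with loss of consciousness, (4) deep brain stimulation, and (5) expected change in PD medications" and related drug changes. Table 1 repeats the criteria with reasons. The phone script in Table A1 covers availability, diagnosis, age, medication plans and brain stimulation, blood draw and contact details, and asks "Have you been diagnosed with any other medical problems (neurological, orthopedic, etc.) that interfere with your ability to do mild body movements". None of these places mentions Qigong experience or earlier study participation.

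The team has run two earlier Qigong studies in Parkinson's disease (sections 1 and 2.1). One is described as follows: "In our feasibility study in a single-arm design (n = 7), a 6-week Qigong exercise program". The other was a pilot randomised trial whose size is not given. Section 2.5 says that recruitment is mainly from one centre, where "approximately 200 new and 1400 returning individuals with PD are seen annually".

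**The concern.** The two arms differ only in components that anyone who has learned this form of Qigong would expect to be taught. A naive participant has no reference point. An experienced one does, and is eligible as the criteria stand.

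Two things can then go wrong in the sham arm:

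- **Loss of blinding.** The participant notices that the sounds, breathing and meditation are absent and infers the allocation. PDSS-2 is a questionnaire about the participant's own sleep, so blinded assessors give no protection. Disappointed expectation would tend to favour Qigong.
- **Contamination.** The participant adds the known components during unsupervised home practice twice a day. This gives the control arm part of the active treatment and pulls the comparison towards no difference. The diary in section 2.1 records whether the exercise was done, other exercise of more than half an hour, symptom scales and free notes, so it would not reliably show this.

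The article itself names missing information on participant blindness as a weakness of earlier trials (section 1). An eligibility gap that weakens blinding is therefore worth closing by the authors' own standard.

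**Working it through.** **1. Is the gap real?** Each place where eligibility is set out was read for prior Qigong or earlier study participation:

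| Place | Content | Prior Qigong or earlier study? |
|---|---|---|
| 2.4.1 | five inclusion criteria | no |
| 2.4.2 | five exclusion criteria | no |
| Table 1 | the same criteria with rationale | no |
| Table A1 | phone script | no |

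The criteria are itemised in full and repeated, so this is not a detail that a condensed article left elsewhere.

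**2. Would an experienced person recognise the sham?** Active exercise: movements, meditation, abdominal breathing and six sounds (3.1, Table 2). Sham: the same movements without the other three (3.2). Someone who knows the six-sounds form would be likely to notice. Someone who knows only yoga, Tai Chi or general meditation has no clear reason to.

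**3. The plan's own sample size.** Inputs from section 5.1: difference 11.5, SD 10.7, power 80%, type I error 0.05 (taken as two-sided).

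n per group = 2 × [(1.96 + 0.84) × 10.7 / 11.5]² = 13.6, so 14. With 30% dropout: 14 / 0.70 = 20. Both stated figures reproduce and are not in dispute. The plan enrols 30 per arm; 30 × 0.70 = 21 remain after dropout.

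**4. Contamination, illustrated.** Assumption, not in the document: 10% to 20% of the sham arm, that is 3 to 6 of 30, practise the full form and gain the full planning effect. The diluted difference is 11.5 × (1 − k/30). Power is for a two-sided t-test at 0.05 with SD 10.7.

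| k of 30 | Difference | Power, 30 per arm | Power, 21 per arm |
|---|---|---|---|
| 0 | 11.5 | 98% | 92% |
| 3 | 10.35 | 96% | 86% |
| 6 | 9.2 | 91% | 78% |

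**5. Unblinding, illustrated.** Assumption: a share f of participants is unblinded and each such contrast is biased by b PDSS-2 points. The group difference shifts by f × b. With 30 per arm the standard error is 10.7 × √(2/30) = 2.76. The value 3.44 is the improvement threshold given in section 4.2; the other values of b, and all values of f, are arbitrary.

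| f | b | Shift | Two-sided type I error (nominal 5%) |
|---|---|---|---|
| 10% | 3.44 | 0.34 | about 5.2% |
| 20% | 5 | 1.0 | about 6.5% |
| 33% | 10 | 3.3 | about 22% |

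**6. Recruitment pool.** Section 2.5 expects about two thirds to qualify: (200 + 1400) × 2/3 = 1,067 patients a year, for 60 places.

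**The case against.** Much of the case on the other side is sound.

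- **The number of experienced enrollees is unknown.** No section says where the earlier studies recruited. The feasibility study had 7 people. If all of them were in the pool of 1,067 and sampled in proportion, 7 × 60/1,067 = 0.4 would enter the trial, about 0.2 in the sham arm. Former participants may volunteer more readily, and the pilot's size is not given, but neither fact supplies a number. This stands.
- **The magnitudes are assumed, and the assumed damage is mostly modest.** A person already practising Qigong may show its effect at baseline and would then not gain a further 11.5 points, so 9.2 is a harsh case. Even there, power is 91% with 30 per arm. The 22% type I error needs a third of participants unblinded with a 10-point bias each. This stands.
- **The two routes act in opposite directions, and randomisation balances prior experience in expectation.** So no net bias is shown. Balance between arms does not, however, prevent recognition of the sham or contamination within the sham arm.
- **The phone script is only an initial screen.** It also omits the cognitive score, Hoehn and Yahr stage, levodopa stability and head trauma, so later screening must exist. But those items are in the formal criteria, and prior Qigong is in neither place.

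A reader might infer that participant blinding fails for the trial as a whole. The document does not support that: the problem is confined to participants who know Qigong, and nothing shows how many would enrol. A reader might also infer that most secondary outcomes share the weakness. They do not. Sections 4.2 and 4.3 list five self-report questionnaires (non-motor symptoms, fatigue, anxiety, depression, quality of life) against seven performance or assay measures (Frontal Assessment Battery, clock test, Trail Making A and B, and three cytokines). Nor does the document support excluding everyone with yoga, Tai Chi or meditation experience, since such experience does not clearly reveal the sham.

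**Conclusion.** The concern holds in limited form. The criteria, Table 1 and the phone script let in people who already know Qigong, including anyone from the team's two earlier studies. For such a person in the sham arm, the stated blinding and the control contrast are at risk on PDSS-2. The share of such people and the net direction of bias cannot be derived from the document. Under the assumed 3 to 6 of 30 contaminated sham participants, the planning difference would shrink by 1.15 to 2.3 points. Under the two milder unblinding assumptions, type I error would rise to about 5.2% to 6.5%. This is a cheap improvement to eligibility. It does not show that the trial's result would be invalid.

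**What to change.** - Add one exclusion criterion to section 2.4.2 and Table 1: participation in either of the team's earlier Qigong studies, or prior training in or regular practice of Qigong.
- Add one matching question to Table A1, worded neutrally so that it does not reveal which components separate the arms, for example by asking about Qigong within a list of activities.
- Record Tai Chi, yoga and meditation practice at baseline as a descriptive variable rather than excluding it.

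The cost is one criterion, one screening question, one baseline item and a slightly smaller pool. With about 1,067 patients a year expected to be eligible for 60 places, the effect on recruitment should be small. No change to the sample size or the analysis follows from this point.

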## 3. Intervention

### 3.1. Experimental Group

The experimental group will learn a specific type of Qigong exercise named ‘six healing sounds’ Qigong. The six healing sounds Qigong exercise consists of mild-body movements, meditation, and abdominal breathing along with uttering six healing sounds. The detailed instruction for the body movements and sounds can be found in Table 2. This form of exercise is chosen because it is appropriate for individuals with PD who may have reduced physical capacity since this exercise is easy to learn and safe to perform. The exercise mainly involves upper mild-body movements and can be performed in any position including standing (preferred), sitting, or lying down. Trained Qigong instructors will lead the 12-week intervention period throughout the study. The format of the Qigong exercise program will be the same over the 12-week intervention.

Participants will be instructed to practice the Qigong exercise at home twice a day in the morning after getting up and in the evening before going to bed. A Qigong exercise session usually takes between 15 and 20 minutes to perform. Participants will be asked to record their exercise performance and self-rated levels of pain, fatigue, sleep quality in a daily exercise diary throughout the study. Participants will have a group meeting every week for the first six weeks and every other week for the remaining six weeks. During group meetings, the Qigong instructor will assess the performance of each participant and discuss relevant issues for about an hour. Also, if a participant shows a sign of low adherence to the exercise, the instructor will provide a behavioral coaching to increase the adherence level based on the model of behavioral change [32]. After the completion of the 12-week intervention period, participants will be asked to continue practicing the Qigong exercise twice a day at home and keep an exercise diary. At the end of the 6-month follow-up, participants will return for a follow-up assessment, which is the same as the baseline and post-intervention assessments.

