### 2.2. Specific Aims

Specific aim I. To examine the effects of Qigong exercise on non-motor symptoms in PD.

Primary hypothesis: Participants will have greater improvement in sleep quality after Qigong exercise than the participants after sham Qigong exercise.

Secondary hypothesis I: Participants will have greater improvement in cognitive function, fatigue, anxiety, depression, overall non-motor symptoms, and quality of life after Qigong exercise than the participants after sham Qigong exercise.

Specific aim II. To examine changes in inflammatory biomarkers in serum after practicing Qigong exercise.

Secondary hypothesis II: Participants will have greater reduction in levels of inflammatory biomarkers (IL-1β, IL-6, and TNF-α) after Qigong exercise than the participants after sham Qigong exercise.

Specific aim III. To examine relationships between changes in non-motor symptom scores and changes in the inflammatory status in PD after the intervention (both Qigong and sham Qigong).

Secondary hypothesis III: Changes in non-motor symptom scores will significantly correlate with changes in levels of the inflammatory biomarkers.

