Sleep quality will be measured using the Parkinson’s Disease Sleep Scale-2 (PDSS-2). This 15-item questionnaire addresses issues related to sleep quality, which has been shown to be reliable in identifying issues specific to PD [33]. A lower score indicates better sleep quality. The minimal clinically important difference (MCID) is the threshold of −3.44 points for detecting improvement or the threshold of 2.07 points for detecting worsening [34].Cognitive function will be assessed using standardized clinical testing methods. The Frontal Assessment Battery evaluates executive function including conceptualization, mental flexibility, programming, sensitivity to interference, inhibitory control, and environmental autonomy [35]. Its maximum score is 18. A higher score indicates better performance. The ten-point clock test will be used to evaluate cognitive deficits. In this test, participants will draw a round-faced clock with hands at ten past eleven. Scoring will be performed using the criteria by Manos and Wu (1994) [36]. The trail making test parts A and B will assess visual attention and task switching. In these tests, participants will connect a set of dots as quickly as possible. The completion time will be compared with normative data [37].Comprehensive non-motor symptoms in PD will be measured by the Parkinson’s Disease Non-Motor Symptom Questionnaire [38]. The assessment contains a total of 30 items including 10 domains (gastrointestinal tract symptoms, urinary tract symptoms, sexual function, cardiovascular symptoms, apathy/attention/memory, hallucinations/delusions, depression/anxiety/anhedonia, sleep/fatigue, pain, and miscellaneous (diplopia, weight loss, etc.)). A lower total score indicates milder PD symptoms.Fatigue level will be measured by the 16-item Parkinson Fatigue Scale, which has shown reasonably good reliability and validity in testing fatigue specific to PD [39]. Its maximum score is 90. A lower score indicates better symptoms.Anxiety and depression will be measured using the 20-item Geriatric Anxiety Inventory and 15-item Geriatric Depression Scale [40,41]. For both scales, a lower score indicates less anxiety or depression.The severity of PD motor and non-motor symptoms will be assessed by the Movement Disorder Society—Unified Parkinson’s Disease Rating Scale (UPDRS) [42]. This assessment consists of four parts including non-motor experiences of daily living (13 items), motor experiences of daily living (13 items), motor examination (18 items), and motor complications (6 items). A lower score indicates milder PD symptoms. The MCID is 2.5 points for detecting minimal improvement in the motor score and 4.3 points for observing minimal improvement in the total score [43].Quality of life will be evaluated using the 39-item Parkinson’s Disease Questionnaire [44]. This assessment covers eight dimensions, including mobility, activities of daily living, emotional well-being, stigma, social support, cognition, communication, and bodily discomfort. A lower score indicates better quality of life. The MCID of sub- and overall-scores suggested by Peto et al. (2001) will be utilized [45].

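### Adherence coaching is written into the Qigong arm only, so following the text as printed adds a co-intervention that the sham does not match

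*Protocol article*

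**What the plan says.** For the Qigong arm, Section 3.1 of the protocol article sets a triggered procedure at the group meetings: "if a participant shows a sign of low adherence to the exercise, the instructor will provide a behavioral coaching to increase the adherence level". It ties this coaching to a cited model of behavioural change.

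For the sham arm, Section 3.2 gives the purpose of the control: "To match with the experimental group in terms of the intensity of activities and duration of the study". On meeting content it says "the sham Qigong instructor will assess the performance of each participant and discuss relevant issues that are the same topics" as in the experimental arm, for about an hour. On home practice it says "This group will be asked to practice the sham Qigong exercise twice a day at home and keep an exercise diary". The difference in exercise content that it declares is that "participants in the control group will not be taught abdominal breathing techniques with six healing sounds and meditation during the exercise".

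Section 2.1 sets the home dose in both arms: "all participants will be asked to perform their assigned exercise (Qigong or sham Qigong exercise) twice a day at home". The primary hypothesis in Section 2.2 is "Participants will have greater improvement in sleep quality after Qigong exercise than the participants after sham Qigong exercise". Section 4.2 measures sleep with the PDSS-2: "This 15-item questionnaire addresses issues related to sleep quality".

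**The concern.** The sham shares the body movements with Qigong, so that the contrast isolates breathing, sounds and meditation. That works only if the shared part is practised about equally in both arms. Coaching is aimed directly at the amount of practice. Given in one arm, it adds practice of the shared movements and extra individual attention from the instructor in that arm alone.

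The difference arises after assignment, so randomization does not remove it, and blinded assessors do not equalise practice. The primary outcome is a questionnaire, which may also respond to attention. Section 2.4.3 makes failure to comply with the exercise a ground for withdrawal in either arm, so one-sided coaching could also affect who stays in the trial. The likely direction favours Qigong.

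**Working it through.** **1. The two arms side by side**

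| Element | Qigong (3.1) | Sham (3.2) |
|---|---|---|
| Weekly meetings for six weeks, then every other week | yes | yes |
| Instructor assesses each participant | yes | yes |
| Discussion of issues, about an hour | yes | yes, same topics |
| Home practice twice a day, with diary | yes | yes |
| Coaching when adherence is low | yes | not stated |
| Breathing, sounds, meditation | yes | no, declared |

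The agreement on topics covers what is discussed at meetings. Section 3.1 introduces coaching separately, as an individual action with its own trigger. The shared procedures in Section 2.1 and the Figure 1 legend do not mention coaching.

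**2. The plan's own figure**

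Inputs from Section 5.1: difference 11.5 points, pooled SD 10.7, power 80%, type I error 0.05 (taken as two-sided), dropout 30%.

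- n per arm = 2 × (1.960 + 0.842)² × (10.7/11.5)² = 13.6, rounded up to 14.
- With dropout: 14/(1 − 0.30) = 20.

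Both match the article. Its 30 per arm is a deliberate increase for the secondary hypotheses.

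**3. How much bias would matter**

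The documents give no coaching rate and no coaching effect, so these are thresholds, not estimates. The model is a two-sample t-test with noncentral t, no true Qigong effect, and a bias of b points.

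- 30 per arm: SE = 10.7 × √(2/30) = 2.76, df 58.
- 21 per arm (30 × 0.70): SE = 10.7 × √(2/21) = 3.30, df 40.

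| Bias b (points) | Rejection rate, 30 per arm | Rejection rate, 21 per arm |
|---|---|---|
| 0 | 5% | 5% |
| 1.0 | 6.5% | 6.0% |
| 2.0 | 11.0% | 9.1% |
| b that gives 10% | 1.83 points | 2.21 points |

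The 1.83 points are 1.83/3.44 = 53% of the improvement MCID in Section 4.2 and 1.83/11.5 = 16% of the planning difference.

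**4. What bias coaching might produce (assumption)**

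Take bias = arm-wide gain in adherence × PDSS-2 benefit of full adherence, and assume a gain of 5 to 20 percentage points. The prescribed dose is 12 × 7 × 2 = 168 home sessions, so 10 percentage points is about 17 sessions.

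- Benefit 3.44 points: 0.05 × 3.44 = 0.17 to 0.20 × 3.44 = 0.69 points, a rejection rate of 5.0% to 5.7%.
- Benefit 11.5 points: 0.05 × 11.5 = 0.58 to 0.20 × 11.5 = 2.3 points, a rejection rate of 5.5% to 13%.

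The second line is an outer bound. The 11.5 points are a pilot difference between Qigong and control, so they are not a fair value for the benefit of the shared movements alone.

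**The case against.** Section 3.2 is a shortened parallel of Section 3.1. It also leaves out the time of day for practice, the diary contents, the session length and the permitted positions, and nobody infers that these differ by arm. Where a difference in exercise content is intended, the article states it, and nowhere does it withhold coaching from controls. A journal article condenses a fuller protocol, and instructor procedures may well sit in a manual. The diaries in both arms would reveal an adherence imbalance.

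The thresholds would apply to any bias in a trial of this size, and they use a t-test where Section 5.2 plans a three-time-point mixed ANOVA with disease duration as covariate. If full practice is worth 3.44 points, a bias of 1.83 points needs an arm-wide adherence gain of 53 percentage points, which coaching of low adherers alone is unlikely to produce.

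Much of this stands. Silence does not prove that coaching is withheld, the numbers do not measure coaching, and doubling of the error rate is improbable through extra shared practice alone. But the comparison with other omissions is incomplete. Time of day and diary contents are given for all participants in Section 2.1, while session length and positions merely describe the exercise. Coaching is an active rule, printed for one arm with a trigger, a deliverer and a theoretical basis. The point concerns a rule stated for one side, not a detail left to another document. Diaries can show an imbalance but do not prevent it.

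**Conclusion.** The concern holds. As written, the plan gives an adherence co-intervention to the Qigong arm and none to the sham arm, contrary to its own aim of matching intensity.

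The size cannot be derived from the document. A modest bias towards Qigong is expected, because coaching reaches only those with low adherence. Under the more plausible assumption in the working (a 5 to 20 percentage-point gain and a benefit of 3.44 points), the bias is about 0.2 to 0.7 points, and the outer bound is 2.3. These ranges rest on an assumed adherence gain, a linear dose-response and a simple t-test, and they leave out any effect of attention or of differential withdrawal. The point does not invalidate the trial or change the sample size. It should be corrected because the confounding is avoidable and the correction is small. Confidence is medium, since coaching may in practice be given in both arms.

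**What to change.** Add to Section 3.2 the coaching rule of Section 3.1: the same trigger for low adherence and the same coaching content, delivered by the sham instructor. Summarise the number of coaching contacts and the diary adherence by arm. If both arms are already coached, the added sentence simply records it.

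A minor clarification can be made at the same time: state that the sham arm's home practice and diary run to the 6-month visit, as Section 3.1 does for Qigong.

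The cost is a short shared coaching script and slightly more work for the sham instructor. Instructors, meetings and diaries already exist in both arms, so no visits or staff are added.
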